## Abstract

*Background.* Atrial fibrillation (AF) is the most common form of arrhythmia. Several trials have suggested that acupuncture may prevent AF. However, the efficacy of acupuncture for AF prevention has not been well investigated. Therefore, we designed a prospective, two-parallel-armed, participant and assessor blinded, randomized, sham-controlled clinical trial to investigate acupuncture in persistent AF (ACU-AF). *Methods.* A total of 80 participants will be randomly assigned to active acupuncture or sham acupuncture groups in a 1 : 1 ratio. Both groups will take the same antiarrhythmic medication during the study period. Patients will receive 10 sessions of acupuncture treatment once a week for 10 weeks. The primary endpoint is AF recurrence rate. Secondary endpoints are left atrium (LA) and left atrial appendage (LAA) changes in function and volume, and inflammatory biomarker changes. *Ethics.* This study protocol was approved by the institutional review boards (IRBs) of Kyung Hee University Hospital (number 1335-04). This trial is registered with clinicaltrials.gov NCT02110537.

## 1. Introduction 

Atrial fibrillation (AF) is the most common form of arrhythmia seen in clinical practice. AF prevalence is 0.4–1% in the general population and increases with age. AF prevalence is 3.8% in people >60 years and 9.0% in those >80 years [1, 2].

The American College of Cardiology (ACC) and American Heart Association (AHA) suggest catheter ablation as standard therapy for patients with symptomatic paroxysmal AF who do not respond to single antiarrhythmic drug (AAD) therapy. However, the effectiveness of catheter ablation is low for patients with persistent AF [2–4]. Therefore, the mainstay therapy for these patients has been long-term AAD, even though persistent AF is poorly controlled by AAD therapy. Electrical cardioversion (EC) is also recommended by the ACC when patients do not respond to AADs [3]. However, the ADD preventive effect on AF recurrence after successful EC is substantially low.

Acupuncture is a nonpharmacological therapeutic intervention widely used in the east. Some experimental studies suggest that the mechanism of acupuncture effects on cardiovascular dysfunction including AF, myocardial ischemia, hypertension, and hypotension is pleiotropic, including pain relief, effects on autonomic nervous system and endothelial function, antithrombotic effects, and decrease of oxygenation stress [5, 6]. Similarly, several clinical studies [7–9] showed that acupuncture seemed to be effective for preventing cardiac arrhythmias, but they were of low methodological quality. A recent, small prospective study [10] reported that patients treated with once-per-week acupuncture for 10 weeks after EC were 2.77 times less likely to experience AF recurrence compared to sham acupuncture or no treatment groups. However, there were issues regarding study design and methodology, including AF detection and follow-up. Thus, there is little evidence to recommend acupuncture as an AF treatment option.

Therefore, this trial evaluates the effect of acupuncture on AF recurrence after EC for persistent AF patients who do not respond to AADs.

## 2. Methods/Design

### 2.1. Patient Population and Study Design

This acupuncture in persistent AF (ACU-AF) study will be a multicenter, prospective, participant and assessor blinded, randomized, sham-controlled clinical trial with 2 parallel arms. Two institutes will take part in this study: Kyung Hee University Medical Center and Kangdong Kyung Hee University Hospital. Eighty patients will be enrolled for 2 years. We will compare the efficacy of active acupuncture and sham acupuncture treatments.

Inclusion and exclusion criteria are listed in Table 1. Flow diagram is displayed in Figure 1. The following data will be evaluated at baseline: demographic data, electrocardiographic and echocardiographic data, comorbidities, biomarkers, medications, and CHA2DS2-VASc score. AAD (flecainide 75 mg twice daily) will be administered to patients confirmed with persistent AF lasting more than 7 days. Flecainide administration will be initiated 2 weeks before EC and maintained during the follow-up period. The resistance for flecainide is defined as AF is not converted to sinus rhythm with oral flecainide before EC. Other types of AADs are not allowed, so participants taking other drugs will be required to change their medication to flecainide. Heart rate control drugs will be permitted (calcium channel blockers such as verapamil or diltiazem, except digoxin and beta blocker), and all dose increases or decreases will be determined by an attending physician. Simultaneous anticoagulation therapy with warfarin will be performed to achieve the target international normalized ratio (INR) of prothrombin time (range 2-3) before EC and during the follow-up period. Patients resistant to drug therapy will be randomized into active and sham acupuncture groups through central randomization. After randomization, once-per-week active or sham acupuncture will be initiated 2 weeks before EC.

Transesophageal echocardiography (TEE) will be conducted just before EC to rule out atrial thrombus and evaluate heart function. If any thrombus is present, EC will be delayed for 2 weeks. In this event, TEE will be conducted again after continuous warfarin administration for 2 weeks. If the thrombus disappears in that time, or is not present, EC will be performed.

EC will be conducted with direct-current electrical shocks. Drugs such as propofol or pentothal sodium (1.5 mg/kg) will be used for patient sedation before the procedure [3]. One electrode pad will be located in the 2nd intercostal, to the right of the sternum, and another will be located in the 5th intercostal beside the central axilla line. EC will start at biphasic waveform 100 J and increase to 200 J until restoration of sinus rhythm. If rhythm is converted to sinus rhythm, the patient will receive an additional 8 interventions once per week. If not, the patient will be dropped from the study. But, if clinically acceptable, a second EC will be performed within 2 months after the first.

In summary, this trial will consist of three periods: 2 weeks of observation and medical therapy, 10 weeks of active or sham acupuncture, and 4 weeks of follow-up for a total of 16 weeks. After randomization, participants will receive 10 acupuncture treatments over 10 weeks. Patients will visit the hospital during randomization, every week before EC, 8 consecutive weeks after EC, and 12 weeks after EC. During the follow-up period, patients whose AF is not converted to sinus rhythm with repetitive EC during the follow-up period will be excluded from this study.

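### Flecainide is dated to start at the same point as post-randomisation acupuncture, leaving no time to establish the flecainide resistance that randomisation requires

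*Protocol article*

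**What the plan says.** All the timing rules are in section 2.1 of the protocol article.

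- Drug start: "Flecainide administration will be initiated 2 weeks before EC and maintained during the follow-up period".
- Resistance: "The resistance for flecainide is defined as AF is not converted to sinus rhythm with oral flecainide before EC". Table 1 lists flecainide resistance as inclusion criterion 3.
- Entry to randomisation: "Patients resistant to drug therapy will be randomized into active and sham acupuncture groups through central randomization".
- Acupuncture start: "After randomization, once-per-week active or sham acupuncture will be initiated 2 weeks before EC".
- Number of sessions: "After randomization, participants will receive 10 acupuncture treatments over 10 weeks". After a successful cardioversion, "If rhythm is converted to sinus rhythm, the patient will receive an additional 8 interventions once per week".
- Visits: "Patients will visit the hospital during randomization, every week before EC, 8 consecutive weeks after EC, and 12 weeks after EC".
- Overall schedule: "2 weeks of observation and medical therapy, 10 weeks of active or sham acupuncture, and 4 weeks of follow-up for a total of 16 weeks".

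Section 2.6 analyses recurrence over a 12-week follow-up. The Discussion (section 3) places the outcome assessment 4 weeks after acupuncture ends.

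**The concern.** The rules imply a fixed order: start flecainide, observe that AF persists, randomise, begin acupuncture. The first and last steps carry the same date, so nothing is left for the two between them. A site that kept to the stated dates would either randomise patients whose resistance had not been tested or depart from the text.

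This matters because the Introduction describes the target population as patients in whom antiarrhythmic drugs have failed, and criterion 3 is what puts that into effect. If the drug and the acupuncture began together, some patients might convert on flecainide after randomisation. A reader of the results could not tell whether resistance had been tested for 2 weeks or not at all.

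**Working it through.** Set EC at week 0.

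**Inputs** (section 2.1 unless noted)

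- Acupuncture: 10 weekly sessions, 8 of them after EC.
- Last visit: week +12. The 12-week follow-up in section 2.6 agrees.
- Schedule: 2, 10 and 4 weeks, stated total 16.
- Flecainide start as written: week -2.
- Acupuncture start as written: week -2, after randomisation.

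**Step 1. Reproduce the stated total.** 2 + 10 + 4 = 16 weeks, as stated.

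**Step 2. Place acupuncture.** Sessions before EC: 10 - 8 = 2. Acupuncture therefore runs from week -2 to week +8, a span of 8 - (-2) = 10 weeks. This matches both the stated acupuncture start and the 10-week period.

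**Step 3. Place the end.** 8 + 4 = week +12. This matches the last visit, section 2.6 and the Discussion.

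**Step 4. Place the first period.** 12 - 16 = week -4. The period of observation and medical therapy therefore occupies weeks -4 to -2.

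**Step 5. Compare the flecainide dates.**

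| Reading | Flecainide start | Flecainide-only time before acupuncture | Flecainide start to last visit |
|---|---|---|---|
| Drug-start sentence as written | week -2 | (-2) - (-2) = 0 weeks | 12 - (-2) = 14 weeks |
| Schedule, if medical therapy means flecainide | week -4 | (-2) - (-4) = 2 weeks | 12 - (-4) = 16 weeks |
| Schedule, if medical therapy excludes flecainide | week -2 | 0 weeks | 14 weeks |

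Every other timing statement fits one calendar. Only the flecainide date leaves no room for the resistance criterion. In the third row the 16-week total can be kept alongside the drug-start sentence, but the flecainide-only interval is still 0.

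**The case against.** The strongest reply is that the document largely answers the point itself. The paragraph makes the intended order plain and the summary puts a 2-week period before acupuncture, so this is one wrong reference point rather than a trial without a run-in. That is fair as to cause: a wording slip is the likely explanation. But the summary shows which date is wrong. It does not correct it, and it does not say that flecainide is the therapy given.

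The other objections:

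- **Resistance could be judged up to EC.** The definition taken alone allows this. It would then settle an inclusion criterion after randomisation, during acupuncture, which contradicts the rule that patients are already resistant when randomised.
- **14 against 16 weeks is not a contradiction in its own right.** This stands. The document never says that flecainide lasts 16 weeks, and warfarin or rate control could fill the first period. The mismatch helps to locate the intended date, but the finding rests on the two identical start dates.
- **Some patients may already have failed flecainide.** The text does not say whether earlier failure counts, so assessment is not shown to be impossible for every patient. For those newly started or switched to flecainide, who are the patients the paragraph describes, no interval exists.
- **A thrombus delays EC by 2 weeks.** Transesophageal echocardiography is done just before EC, when acupuncture is already under way, so the delay adds no time before randomisation.
- **Figure 1 or a fuller protocol may show the run-in.** Neither is available here. Even if one did, the article would still carry an explicit drug-start date that conflicts with it.
- **The consequences are small.** Both arms have the same drug schedule. This limits the severity but does not remove the error.

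**Conclusion.** The concern holds. Section 2.1 gives three rules that cannot all be followed for a patient starting flecainide: drug start at week -2, resistance established before randomisation, and post-randomisation acupuncture at week -2. The flecainide-only interval is 0 weeks as written. It is 2 weeks under the 16-week schedule, on the assumption that its medical therapy includes flecainide. That is the natural reading, because flecainide is the drug whose failure decides entry. If the assumption fails, the interval is still 0, so the main conclusion does not depend on it.

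This is a misdated rule that should be corrected, because it governs who enters the trial. No imbalance between arms and no effect on sample size, power or the primary analysis is claimed.

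**What to change.** In section 2.1, state that flecainide starts 2 weeks before randomisation, that is, 4 weeks before planned EC, and continues through follow-up. This restores 2 weeks in which to assess resistance, and the 16-week total then runs from drug start to last visit.

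A useful clarification, though not needed to remove the conflict, is to define resistance as AF still present on a 12-lead ECG at the end of those 2 weeks and before randomisation, in place of a definition tied only to EC.

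The cost is two sentences. If the sites already follow the 16-week schedule, there is no operational change.

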### 2.4. Outcome Measurement 

#### 2.4.1. Primary Endpoint

Primary endpoint is AF recurrence rate after EC using regular 12-lead electrocardiography (ECG) and 48-hour Holter monitoring. ECG will be conducted at each visit. Whenever patients feel palpitation, symptoms must be registered and patients must be referred to the hospital. AF recurrence is defined as documented 12-lead ECG or AF episodes exceeding 30 seconds during Holter monitoring. 48-hour Holter will be performed at day 1 after EC at baseline and 1 and 3 months post-EC to evaluate recurrence.

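### Two post-randomisation removal rules around electrical cardioversion (EC) leave the primary comparison in a subset that treatment could shape, and one can remove patients who already have the primary event

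*Protocol article*

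**What the plan says.** All of the following is in the protocol article.

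- **Randomisation comes before EC** (section 2.1): "Patients resistant to drug therapy will be randomized into active and sham acupuncture groups through central randomization".
- **Allocated treatment also comes before EC** (section 2.1): "After randomization, once-per-week active or sham acupuncture will be initiated 2 weeks before EC". Two of the ten weekly sessions are therefore given before the shock.
- **Remaining sessions depend on conversion** (section 2.1): "If rhythm is converted to sinus rhythm, the patient will receive an additional 8 interventions once per week".
- **First removal rule** (section 2.1): "If not, the patient will be dropped from the study". The next sentence qualifies it: "But, if clinically acceptable, a second EC will be performed within 2 months after the first".
- **Second removal rule** (section 2.1, closing summary): "patients whose AF is not converted to sinus rhythm with repetitive EC during the follow-up period will be excluded from this study".
- **Endpoint** (section 2.4.1): "Primary endpoint is AF recurrence rate after EC". The Conclusion likewise frames the question as recurrence once EC has restored sinus rhythm.

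The sample size section allows 20% for dropout in general. It does not say whether EC failures are part of that allowance. Nothing in the article keeps removed patients in follow-up or gives them an outcome.

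**The concern.** Whether EC restores sinus rhythm is observed after allocation and after two sessions of allocated treatment, so it is an outcome that treatment could affect. The article's own rationale makes this possible: the Introduction and Discussion credit acupuncture with autonomic and antiarrhythmic actions. If these act before EC, the converters in the two arms are different kinds of patient, and randomisation no longer protects the comparison between them.

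The second rule adds a separate problem. A patient who converts, relapses into AF and then fails a repeat EC has had the primary event. Read as written, the rule takes that patient out of the study.

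At stake is the validity of the primary comparison. The loss may also be permanent, because an analysis plan cannot restore the 12-week status of patients who were no longer followed.

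**Working it through.** **1. The plan's own figure.** Inputs from section 2.5: recurrence 35.3% active and 69.2% sham, 5% two-sided, 80% power. With the pooled normal formula,

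n = [1.96·√(2p̄(1−p̄)) + 0.8416·√(p₁(1−p₁)+p₂(1−p₂))]² / (p₁−p₂)²

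where p̄ = (0.353 + 0.692)/2 = 0.5225. This gives 2p̄(1−p̄) = 0.4990, p₁(1−p₁)+p₂(1−p₂) = 0.4415, and n = 3.778/0.339² = 32.9, so 33 per arm. The stated figure is reproduced, with power of 80.2% at 33. The issue is who is analysed, not the arithmetic.

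**2. How far selection could move the result.** The documents give no EC failure rate, so every input here is assumed:

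- Acupuncture has no effect on recurrence in any patient.
- Patients who convert under either allocation (always-converters) recur at 65%.
- Patients who convert only in the arm with fewer failures (marginal converters) recur at 95%.

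Recurrence among converters in an arm = (always-converters × 0.65 + marginal converters × 0.95) / all converters.

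| EC failure, active v sham | Active converters | Sham converters | Spurious difference |
|---|---|---|---|
| 10% v 20% | (0.80×0.65 + 0.10×0.95)/0.90 = 68.3% | 65.0% | +3.3 points, against active |
| 10% v 30% | (0.70×0.65 + 0.20×0.95)/0.90 = 71.7% | 65.0% | +6.7 points, against active |
| 20% v 10% | 65.0% | 68.3% | −3.3 points, favouring active |

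Keeping everyone in the first row and counting failed EC as an event gives:

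- active: 0.10 + 0.90×0.683 = 71.5%
- sham: 0.20 + 0.80×0.65 = 72.0%

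The apparent harm disappears. For scale, the planned difference is 69.2 − 35.3 = 33.9 points. If EC failure does not depend on treatment, no such bias arises from the first rule.

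**3. What each analysis set costs in power.** EC failure f is assumed equal in both arms, with 40 randomised per arm and no other dropout. For converters only, n = 40(1−f) at 35.3% v 69.2%. For all randomised, n stays 40 and each rate becomes f + (1−f)p.

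| f | Converters only: n per arm, power | All randomised: rates, power |
|---|---|---|
| 5% | 38, 85.6% | 38.5% v 70.7%, 83.8% |
| 10% | 36, 83.6% | 41.8% v 72.3%, 79.9% |
| 15% | 34, 81.4% | 45.0% v 73.8%, 75.6% |
| 20% | 32, 78.9% | 48.2% v 75.4%, 71.2% |

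With no EC failure and no dropout, power at 40 per arm is 87.3%. For 80% power, the all-randomised analysis needs 37, 41, 45 or 50 per arm, again before other dropout.

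**The case against.** **The second EC.** A reader might infer from the first rule that every patient who fails EC is lost. The documents do not say that, since a second EC within 2 months is permitted and some first failures may stay in. This limits the loss but does not remove the problem. The second attempt is discretionary, the article gives no time origin or session schedule for a patient converted that way, and a patient who still does not convert goes.

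**The question is recurrence after conversion.** This is a legitimate question, and recurrence has no meaning in a patient who never converted. Counting failed EC as an event does change the endpoint, and that should be stated openly. But randomisation protects a converters-only comparison only if treatment before EC does not affect who converts, and here two sessions precede it.

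**The analysis set may be in the SAP.** The article names no analysis set, and that omission is not the point. The removal rules are stated design instructions, and the converters-only comparison follows from applying them as written.

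**Blinding and a set shock sequence.** Blinding of participants and assessors and a fixed energy escalation limit differential handling. They do not prevent selection through a real treatment effect.

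**Power.** A reader might also infer a power of about 74%, from 10% EC failure on top of 20% dropout: 40 × 0.9 × 0.8 = 28.8 per arm. That stacking is an assumption. The article calls failed-EC patients dropped, so its 20% dropout may already include them. If it does, 32 per arm remain and power is 78.9%.

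**Conclusion.** The concern stands as a defect of design. Two stated rules remove randomised patients on grounds that arise after allocation, and the primary comparison is then conditional on events that treatment could change. The second rule can also remove patients who have already reached the endpoint.

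Confidence is high for the mechanism and low for its size. The spurious difference of about 3 to 7 points rests on the assumed failure rates and recurrence risks above, and it can run in either direction. The documents do not support saying that the result will be biased, that its sign will reverse, or that it will favour a particular arm. Bias from the first rule needs acupuncture to change who converts. If it does not, that rule costs precision only.

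**What to change.** 1. Replace both removal rules with one statement: a patient who is not converted, at first or on repeat EC, may leave study treatment as the clinicians decide but remains in follow-up and in the analysis.
2. Make all randomised patients the primary analysis set, and count AF not converted by EC as an event.
3. State in advance how three groups are classified: patients converted by the permitted second EC, patients already in sinus rhythm before EC, and patients whose EC is not done (for example because of thrombus).
4. State that no patient is excluded after a documented recurrence.
5. Report conversion by arm, and keep the converters-only comparison as a sensitivity analysis.
6. Reconcile the section 2.1 statements on dropping after failed EC, on a second EC, and on exclusion after repeat EC. Clinical management of unconverted patients, including whether a second EC is done, stays with the clinicians.

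**Cost.** The work is amendment wording plus outcome follow-up for patients who would otherwise have left. The statistical cost is real. The endpoint becomes AF persisting or recurring, and at equal EC failure of 5%, 10%, 15% or 20% power at 40 per arm is about 84%, 80%, 76% or 71% before other dropout. The sponsor should restate the power with an explicit EC failure assumption, and say whether the 20% dropout allowance includes EC failures.

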### 2.6. Statistical Analysis

Demographic data will be analyzed to identify pretreatment equivalencies and differences between the two groups. Continuous variables will be presented as mean ± standard deviation (SD), evaluated for distribution normalcy, and compared using the Student's *t*-test or Mann-Whitney test wherever appropriate. Categorical variables will be presented as frequencies and percentages and compared using chi-squared or Fisher's exact tests wherever appropriate. AF recurrence during the 12-week follow-up will be analyzed with Kaplan-Meier curves.

Multivariate Cox regression analysis will be performed to determine which factor is most strongly associated with AF recurrence. Serious adverse events will be tabulated per treatment group and analyzed using the chi-squared test.

A *P* value less than 0.05 will be considered statistically significant. All analyses will be performed with SPSS software (Windows version 17.0, Chicago, Illinois, USA) by a statistician blinded to participant allocation.

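### Randomised, already treated patients are excluded according to their rhythm after repeat cardioversion, and no time origin is set for patients who have a second cardioversion

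*Protocol article*

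**What the plan says.** All of the following is in the protocol article.

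- **Order of events (section 2.1).** "After randomization, once-per-week active or sham acupuncture will be initiated 2 weeks before EC". Every patient who reaches EC is therefore already randomised and treated.
- **First EC fails (section 2.1).** "If not, the patient will be dropped from the study". The next sentence adds: "But, if clinically acceptable, a second EC will be performed within 2 months after the first".
- **Repeat EC fails (section 2.1).** "patients whose AF is not converted to sinus rhythm with repetitive EC during the follow-up period will be excluded from this study".
- **Visits and length (section 2.1).** "Patients will visit the hospital during randomization, every week before EC, 8 consecutive weeks after EC, and 12 weeks after EC". The final period is "4 weeks of follow-up for a total of 16 weeks".
- **Endpoint (section 2.4.1).** "Primary endpoint is AF recurrence rate after EC using regular 12-lead electrocardiography (ECG) and 48-hour Holter monitoring". AF on a 12-lead ECG, or for more than 30 seconds on Holter, counts as recurrence. Holters are timed from EC.
- **Analysis (section 2.6).** "AF recurrence during the 12-week follow-up will be analyzed with Kaplan-Meier curves".

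The article does not say whether a recurrence recorded before exclusion still counts, or which EC starts the visits, the Holters and the 12 weeks. Follow-up means 4 weeks in section 2.1 and 12 weeks in section 2.6.

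**The concern.** A rule that removes randomised patients because of the rhythm they are in makes membership of the analysis depend on the outcome. Three things are at stake:

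- Recorded recurrence would be too low and events would be lost, in a trial of only 80 patients.
- The comparison would no longer be protected by randomisation. If the share of patients excluded differs between arms, a difference can appear where there is none. The second EC is discretionary and no criterion is given for offering it.
- Kaplan-Meier curves need one start point. For anyone with a second EC, neither the start nor the remaining time at risk is fixed.

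**Working it through.** **1. The plan's own figure.** Inputs from section 2.5: 35.3% active, 69.2% sham, two-sided 5%, 80% power. With pooled variance under the null and no continuity correction:

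n = [1.960 × √(2 × 0.5225 × 0.4775) + 0.842 × √(0.353 × 0.647 + 0.692 × 0.308)]² / 0.339² = 32.9, so 33 per group, as stated.

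With 40 per group and the planned 20% dropout, 40 × 0.80 = 32 per group remain; power is 0.789.

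**2. Equal exclusion in both arms.** Let *p* be the true recurrence rate and *f* the share of recurrences that end in failed repeat EC and exclusion. The article gives no *f*, so 10% to 30% is an assumption. This step takes the reading in which the excluded patients had recurred and their events are not kept. The recorded rate is *p*(1 − *f*)/(1 − *pf*), and the number left is 32(1 − *pf*).

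| *f* | Removed, active / sham | Recorded rate, active / sham | Difference | Power |
|---|---|---|---|---|
| 0 | 0 / 0 | 35.3% / 69.2% | 0.339 | 0.789 |
| 10% | 1.1 / 2.2 | 32.9% / 66.9% | 0.340 | 0.767 |
| 30% | 3.4 / 6.6 | 27.6% / 61.1% | 0.335 | 0.708 |

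About twice as many patients leave the sham arm, because more recur there, yet the risk difference hardly moves. The cost is understated rates and lost events.

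The starting number matters. From 40 per arm with no other loss, power is 0.873 without exclusions, 0.856 at 10% and 0.804 at 30%.

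**3. Unequal exclusion with no true effect.** Assume a true 50% in both arms (16 of 32), with 30% of active and 10% of sham recurrences excluded:

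- Active: (16 − 4.8)/(32 − 4.8) = 11.2/27.2 = 41.2%
- Sham: (16 − 1.6)/(32 − 1.6) = 14.4/30.4 = 47.4%

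This is a false benefit of 6.2 percentage points, and the nominal 5% two-sided error becomes about 7.5%. Reversing the split reverses the sign.

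**4. The clock.** Two months is about 8.7 weeks. The planned path is 2 weeks of observation + 2 weeks of sessions before EC + 12 weeks after EC = 16 weeks.

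- Clock stays on the first EC: 12 − 8.7 = 3.3 weeks remain after a second EC at the limit.
- Clock restarts at the second EC: 16 + 8.7 = 24.7 weeks in total, against the stated 16.

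**5. Sessions.** Section 2.1 places 10 treatments in the 10 weeks after randomisation, and also gives 8 further sessions once sinus rhythm is restored. A second EC at the limit falls about 2 + 8.7 = 10.7 weeks after treatment starts. For that patient the two statements cannot both hold.

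**The case against.** The strongest reply is that the excluded patients may have no recurrence to lose. The only repeat EC described in the article follows a failed first one, and an EC within 2 months falls inside the 12 weeks. The exclusion sentence can therefore be read as the end of that pathway, covering patients never converted. The Conclusion (section 4) frames the question as recurrence after conversion. This stands as a possible reading, and on it the calculation in step 2 does not apply. The rule would still remove randomised, treated patients because of their rhythm.

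Exclusion might also mean only that further follow-up stops, with earlier events kept, and analysis sets are commonly left to a document not shown here. That is fair, so a reader who infers that events are certainly deleted goes beyond the text. However, the article does state an exclusion from the study, and an analysis of all randomised patients would have to override or explain it.

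Other stronger inferences are not supported:

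- **That the second EC contradicts the drop rule.** Its sentence is worded as a conditional exception. What is missing is its specification: the patient's status between the two procedures, and when dropping takes effect.
- **That treatment is nearly over by a second EC.** The 8 further sessions follow conversion, so on that sentence they would still lie ahead.
- **That the trial is biased towards acupuncture.** Nothing in the article points to unequal shares. Participants and assessors are blinded, and the acupuncture practitioners are not said to decide on EC. The 30% v 10% split is illustrative only.

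First-EC failures may also already sit within the 20% dropout allowance, so starting from 32 per arm may count some losses twice.

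**Conclusion.** The point holds in this form. The protocol article fixes a post-randomisation exclusion that depends on rhythm, and leaves the time origin open for anyone with a second EC. Both can be read directly from the text.

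The numerical size is conditional. It rests on assumed shares, on the reading that recurrent patients are excluded with their events, and on 32 per arm before these exclusions. With equal shares of 10% to 30%, the loss is about 2 to 8 points of power and 2 to 8 points off each recorded rate, with the difference essentially unchanged. Bias between arms arises only if the shares differ; its size and direction cannot be taken from the article. The timing figures (3.3 weeks left, or 24.7 weeks in total) assume a second EC at the 2-month limit.

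It should be settled before patients are excluded, because outcomes not collected after exclusion cannot be reliably restored at analysis.

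**What to change.** Amend sections 2.1, 2.4.1 and 2.6 to state that:

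1. Stopping study treatment or failing repeat EC does not remove a randomised patient from the primary analysis.
2. The event is the first documented AF after conversion, and a later EC does not cancel it.
3. One time origin applies to every patient, for visits, Holters and the 12-week window alike.
4. Never-converted patients follow an explicit rule. One option is to count them as failures at time zero in an analysis of all randomised patients, with recurrence among converted patients as a supporting analysis. This widens the endpoint from recurrence to treatment failure, and the 35.3% and 69.2% in section 2.5 were stated for recurrence, so the text should say so.

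Reconcile the three sentences on dropping, second EC and exclusion, the two statements on session timing, and the 4-week and 12-week meanings of follow-up. None of this prescribes whether or when EC is repeated.

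The cost is a few amended sentences, with no new procedures. Patients who would otherwise have left need to complete the visits already scheduled. If item 4 is adopted as the primary analysis, the sample size assumptions need a second look.
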